### Engagement for recruitment

We have a multi-pronged approach to optimise recruitment including through lead maternity caregivers (self-employed midwives), community antenatal clinics, general practitioners, practice nurses, ultrasound clinics, community contacts, and social media. Our research team provides educational sessions for the health care providers to maximise reach for recruitment. Lead maternity caregivers notify the research team about contact details of eligible women who are interested in participating. The research midwife arranges a time to meet the woman in a suitable location to explain the study, confirm eligibility and obtain informed consent.

In order to exclude women with previously unrecognised Type 2 diabetes, HbA1c is measured in all participants (using the Roche cobas b 101 point-of-care system) prior to randomisation. If HbA1c is ≥50 mmol/mol, women are ineligible and considered to have undiagnosed diabetes [50]. They will be referred to the Diabetes in Pregnancy Service at CMH. If the HUMBA point of care HbA1c is <50 mmol/mol, then the result is not revealed to health practitioners.

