#### 1st assessment visit (12^0^ – 17^+6^ weeks)

Confirmation of eligibility, informed consent, and randomisation is conducted at the first assessment visit. Comprehensive information is obtained from the woman and her clinical records, including: demographic, socioeconomic, educational and employment data; medical history; obstetric history such as parity, method of conception, gestation and accuracy of estimated date of delivery, previous pregnancy complications (GDM, hypertensive disease, pre-term delivery, caesarean section); family history of diabetes, hypertension and cardiovascular disease; history of smoking, alcohol and other drug use; medications and nutritional supplements; probiotic food ingestion; maternal anthropometrics: weight, height, waist and mid-arm circumference; blood pressure (BP); finger-prick blood lipid testing (Roche cobas b 101 point-of-care system); samples collection : non-fasting blood and urine specimen for biobank; questionnaires including: New Zealand Food Frequency Questionnaire - Short Form [59], New Zealand Physical Activity Questionnaire [60], Edinburgh Postnatal Depression Scale (EPDS) [61], State-Trait Anxiety Inventory (STAI) [62], and the 12-item Short-Form Health Survey (SF-12) [63]. It takes approximately 30 min to complete these questionnaires.

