#### 2^nd^ assessment visit (28–30 weeks)

All women in the HUMBA trial are requested to have an OGTT at 26–28 weeks. The second assessment visit is scheduled after the OGTT at approximately 28–30 weeks. Weight, mid-arm circumference and BP are measured. The food frequency, physical activity questionnaires and a fetal movement questionnaire are completed by the participant. The fetal movement questionnaire is adopted from a previous study [64]. An updated medical history is obtained by the research midwife. The OGTT results are reported to the research team with fasting, one- and two-hour results enabling a diagnosis of GDM by the International Association of Diabetes in Pregnancy Study Groups (IADPSG) criteria [65]. The maternity care provider receives fasting and two-hour glucose results from the OGTT as per usual clinical practice using the New Zealand Society for the Study of Diabetes (NZSSD) criteria [66]. Women diagnosed with GDM by the NZSSD criteria will be referred by their maternity care provider to the Diabetes in Pregnancy Service (as per usual practice) and managed according to local guidelines including postpartum testing.

HbA1c and lipid concentrations are measured by finger prick using the Roche cobas b 101 point-of-care system.

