#### 3^rd^ assessment visit (36 weeks)

Weight, mid-arm circumference, BP, and HbA1c and lipid concentrations (Roche cobas b 101 point-of-care system) are measured. Any pregnancy complications to date and use of antibiotics are recorded. The fetal movement questionnaire and functional health and well-being questionnaires including EPDS, STAI and SF-12 are repeated. Maternal urine, blood, stool, toenail clippings and hair samples are collected from consenting women for future molecular biology studies.

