#### 5^th^ assessment visit (5 months postpartum)

A follow up appointment with the research midwife and a paediatrician are scheduled at 5 months (±2 weeks) postpartum. Maternal lifestyle and food frequency questionnaires, and infant health and well-being questionnaires are completed. Measurements of maternal BP, weight, height, waist and mid-arm circumference, and body composition by Bioelectrical Impedance Analysis [68] (ImpSFB7®, ImpediMed, Brisbane, Australia) are undertaken. Data are collected on infant feeding, allergies, health and anthropometry (weight and length; head, left mid-arm, chest and abdominal circumference; subscapular, triceps and suprailiac skinfolds), and body composition by PEA POD®, if consented. Infant feeding behaviours are assessed using the Baby Eating Behaviour Questionnaire (BEBQ) [69], and infant eating patterns and nutritional intake will be determined by a food frequency questionnaire. Timing of assessment will be based on corrected age. Consent will be obtained for ongoing contact when funding is obtained for further follow up.

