### Secondary outcomes

Maternal secondary outcomes include:Maternal pregnancy glucose metabolism as assessed by OGTT parameters at 26–28 weeks [70], and HbA1c at 28 and 36 weeks and 5 months postpartum.Changes in diet quality and dietary patterns between recruitment, 28–30 weeks and 5 months postpartum [59]Functional health and well-being (SF-12) at 36 weeks and 5 months postpartum [63]Depression and anxiety scores at 36 weeks’ and 5 months postpartum [62, 63]Maternal adiposity at 5 months postpartum (assessed by weight, BMI, waist and arm circumference and fat mass measured by bioimpedance)GDM by NZSSD criteria [66]Pregnancy induced hypertension (preeclampsia and gestational hypertension) [71]Mode of birthBlood lipid concentrations at 28–30 and 36 weeks’ gestation and 5 months postpartumMaternal feedback about participation in the study (survey at post birth visit)

Infant secondary outcomes include:Neonatal anthropometry: head circumference and length, and associated Z-scores [72]; birthweight adjusted for length; girths (chest, arm and abdominal) adjusted for length; subscapular, triceps and suprailiac skin fold thickness adjusted for length; and arm muscle area adjusted for arm lengthNeonatal body composition (via PEA POD®) including fat mass and lean mass adjusted for length and fat mass adjusted for lean massGestational age at birthLGA, by customised [73] and population [72] references.Small for gestational age (SGA, <10^th^ centile), by customised [73] and population [72] references.Admission to neonatal care unit (and reason)Neonatal composite morbidity, including birth trauma (fracture, brachial plexus injury, cephalohaematoma, subgaleal haematoma), hypoxic ischaemic encephalopathy, sepsis, respiratory distress requiring continuous positive airway pressure support, hypoglycaemia requiring dextrose treatment (buccal or intravenous)Initiation and establishment of breast feeding, including feeding in first two postnatal weeks (collected by phone call at 6 weeks and questionnaires)Infant anthropometry and body composition at 5 months of age, as detailed aboveInfant feeding over first 5 months (breast feeding, formula use, complementary feeding with solids)Feeding behaviour as assessed by BEBQ scores [69]Infant Nutritional intake at 5 months, estimated from a four day food frequency questionnaire

Other secondary outcomes include:Attendance at study visitsAdherence to probiotic/placebo regimeCost effectiveness of the intervention

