### Statistical analysis plan

Analyses will follow the principle of intention-to-treat. Participants will be analysed according to the assigned treatment group at randomisation. Statistical models will adjust for the key randomisation stratification variable, BMI at recruitment.

Binary endpoints will be analysed using logistic regression to estimate odds ratios for each of the interventions (dietary intervention and probiotics). Continuous outcomes will be modelled using generalised linear models to estimate any changes in outcomes with the interventions (dietary intervention and probiotics) compared to their respective control groups.

Primary analyses will report marginal effects for each randomised exposure, with adjustment for co-intervention, BMI at recruitment (randomisation stratification variable), ethnicity and sex (infant outcomes). We will also test for interactions between the main effects (primary outcomes only), though this pilot trial has been powered only for the main effects.

Sensitivity analyses will be carried out according to compliance with the study interventions (primary outcomes); specifically these will be:Those women who reported taking their probiotics most of the time at all time points (forgot to take 1–3 per month, or greater than 1 per week but not most days at 28 weeks, 36 weeks and birth visits).Those that attended at least 3 out of the 4 dietary education sessions.

Analyses of secondary outcomes involving maternal data collected at recruitment, 36 weeks’ and 5 months’ will be analysed using mixed methods to allow for the repeated measures of these outcomes over time. Measures of infant body composition (whole-body fat and fat-free mass) will be adjusted by infant sex and ethnicity, and skinfold thickness and arm muscle area will additionally be adjusted for infant length. For birth data, analyses will be adjusted for gestational age at birth (weeks). We will explore for an interaction between intervention effect and infant sex.

For the primary outcomes a two-sided alpha level <0.025 will indicate statistical significance (Bonferroni adjustment). For secondary outcomes, a two-sided alpha level <0.05 will indicate statistical significance.

Depending on the proportion and the pattern of missing data, multiple imputation may be used to impute missing data for some exploratory variables (secondary outcomes).

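### The repeated-measures sentence omits the 28–30 week visit, and OGTT glucose is not adjusted for baseline HbA1c: the cost is precision in secondary outcomes, not validity

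*Protocol article*

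**What the plan says.** The Statistical analysis plan section assigns repeated maternal outcomes to a mixed model by naming visits: "Analyses of secondary outcomes involving maternal data collected at recruitment, 36 weeks’ and 5 months’ will be analysed using mixed methods". Other continuous outcomes go to a generalised linear model. The covariates named in that section are the co-intervention, BMI at recruitment, ethnicity and, for infant outcomes, sex. The full list is attached to the primary analyses. No baseline biomarker is mentioned.

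The Secondary outcomes section sets different times for several maternal measures. Glucose metabolism, listed first, comprises OGTT values at 26–28 weeks and "HbA1c at 28 and 36 weeks and 5 months postpartum". Lipids are listed at 28–30 weeks, 36 weeks and 5 months. Diet is given as "Changes in diet quality and dietary patterns between recruitment, 28–30 weeks and 5 months postpartum".

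On collection, the Engagement for recruitment section states that "HbA1c is measured in all participants (using the Roche cobas b 101 point-of-care system) prior to randomisation", for the purpose of excluding unrecognised diabetes. Lipids are tested at the first assessment visit. At the second visit (28–30 weeks), "HbA1c and lipid concentrations are measured by finger prick using the Roche cobas b 101 point-of-care system", and both are measured again at 36 weeks. The 5-month visit lists "Measurements of maternal BP, weight, height, waist and mid-arm circumference, and body composition by Bioelectrical Impedance Analysis", but neither HbA1c nor lipids.

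**The concern.** The three visits named for the mixed model suit the depression, anxiety and SF-12 scores. They do not suit HbA1c and lipids, which also have a 28–30 week value, or diet, which has a 28–30 week value and none at 36 weeks. The text then allows two readings. On one, the visit list is a slip and every visit belongs in the mixed model. On the other, a single biomarker is split: its 28–30 week value goes to a separate cross-sectional model, while its later values go to a longitudinal model that includes recruitment. Secondary outcomes are tested at 0.05 each, so the choice is better fixed before the data are seen.

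The OGTT has no baseline counterpart. HbA1c is the only pre-randomisation measure of glycaemia described, and its only stated use is the eligibility screen. A reduction in gestational diabetes (GDM) is prominent in the Background's case for probiotics, so precision on glucose outcomes matters in a trial with about 100 women per margin.

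**Working it through.** **1. The design figure.** From the Sample size section: 100 per main group, two-sided alpha 0.025, 80% power, birthweight SD 521 g, excessive weight gain 80% versus 60%.
- Birthweight: 521 × √(2/100) × (2.241 + 0.842) = 227.2 g, against 227 g stated.
- Weight gain: 99 per group are needed, and 100 per group give 80.7% power.

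The design reproduces. It rests on the two primary outcomes and does not depend on this point.

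**2. Visits side by side.**

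| Measure | First visit | 28–30 wk | 36 wk | 5 months |
|---|---|---|---|---|
| Mixed-model sentence | named | not named | named | named |
| HbA1c | yes, before randomisation | yes | yes | outcome listed; not in visit description |
| Lipids | yes, order relative to randomisation not stated | yes | yes | outcome listed; not in visit description |
| Diet | yes | yes | no | yes |
| Depression, anxiety, SF-12 | yes | no | yes | outcome listed |

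The sentence covers three of the four times for HbA1c and lipids, two of the three for diet, and all three for the well-being scores. The 28–30 week values that it leaves out are continuous secondary outcomes, so the general model applies to them. For diet the recruitment value already enters through the definition of the outcome as a change. For 28–30 week HbA1c and lipids, and for OGTT glucose, no baseline value is named.

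**3. What a baseline covariate could add.** Adjusting a continuous outcome for a baseline value with correlation r multiplies its residual variance by 1 − r². Inputs: 100 per margin (Sample size section), two-sided alpha 0.05 (the level set for secondary outcomes), 80% power. The article gives no value of r, so the values below are assumptions.

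Detectable difference in SD units = (1.960 + 0.842) × √(2/100) × √(1 − r²) = 0.396 × √(1 − r²).

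| Assumed r | √(1 − r²) | Detectable difference (SD) | Equivalent n per margin, 100/(1 − r²) |
|---|---|---|---|
| 0 | 1.000 | 0.396 | 100 |
| 0.1 | 0.995 | 0.394 | 101 |
| 0.3 | 0.954 | 0.378 | 110 |
| 0.5 | 0.866 | 0.343 | 133 |

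The r = 0 row takes no credit for the BMI adjustment already planned. The formula is for continuous outcomes only. It does not apply to GDM, which is analysed by logistic regression.

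**The case against.** The strongest reply is that little is wrong. The 28–30 week values do have a stated analysis, the generalised linear model. The mixed-model sentence names recruitment, so first-visit HbA1c and lipids already inform the 36-week and 5-month analyses. Randomisation makes the unadjusted comparison valid, and chance imbalance is already reflected in the standard error. Covariates for secondary outcomes are often left to a fuller analysis plan, which is not at hand. The correlation is assumed, and excluding women with HbA1c of 50 mmol/mol or more narrows the range, which may weaken it; at r = 0.1 the gain is negligible. For GDM, adding a prognostic covariate also changes the conditional odds ratio being estimated.

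All of this stands, and it limits the point to precision. It does not remove the mismatch: the article itself fixes a visit list, and that list does not match its own outcome schedule for HbA1c, lipids or diet. Nor does it explain why a value held for every participant should have no role in the glucose analyses.

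A reader might go further and infer that collected biomarker data go unused, or that the glucose results would be biased. The article does not support either. Nothing says that any value is excluded, and the 28–30 week results are named outcomes with a model that covers them. A reader might also take r = 0.7, which gives 0.283 SD, as the gain for HbA1c and lipids at every visit. That would credit the change with precision that the mixed model may already supply at 36 weeks and 5 months.

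**Conclusion.** The point holds as a low-cost improvement to the secondary analyses. The visit list in the repeated-measures sentence does not match the declared times for HbA1c, lipids and diet; this follows from the article alone. Leaving baseline HbA1c out of the OGTT models is a missed gain in precision, not an error. Its size is unknown: from almost nothing (0.394 SD at r = 0.1) to a fall in the detectable difference from 0.396 to 0.343 SD at r = 0.5, mainly for OGTT glucose and the 28–30 week values. This rests on assumed correlations and 100 women per margin.

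Two related matters are open in the text. HbA1c and lipids are 5-month outcomes, but the 5-month visit description lists neither. First-visit lipids are not stated to precede randomisation, as HbA1c is. Primary outcomes and sample size are unaffected.

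**What to change.** - Add 28–30 weeks to the repeated-measures sentence, or list the outcomes and visits that it covers. HbA1c, each lipid and diet would then each be analysed across all their post-randomisation visits, with the first-visit value as baseline.
- State that fasting, one-hour and two-hour OGTT glucose are adjusted for baseline HbA1c. For GDM the adjustment is optional; if it is used, say that the odds ratio is conditional on baseline HbA1c.
- Reconcile the 5-month HbA1c and lipid outcomes with the description of that visit.
- Confirm that first-visit lipids are taken before randomisation.

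The first two changes cost only wording, because the article already describes collection of the first-visit and 28–30 week values and takes HbA1c in all participants. The 5-month item is also wording if those measurements are in fact made; if they are not, either the outcome list or the visit schedule has to change.

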### Randomisation

Randomisation is undertaken using a web-based protocol, randomize.net (http://randomize.net), using random block sizes (minimum 4; maximum 8). For randomisation purposes, each research midwife will serve as a proxy for ‘clinical site’ (this will enable each research midwife to be able to dispense the randomised study capsules at recruitment). Participants are stratified by ‘clinical site’ (n = 2) and BMI category (BMI of 30–34.9 or BMI ≥35 kg/m^2^) and randomly allocated in a 1:1 ratio to dietary intervention or routine dietary advice; and 1:1 ratio to probiotic or placebo (Fig. 1).

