### Sample size and power calculation

A total of 220 participants will be recruited. With 80% power and 100 subjects remaining in each main intervention group (allowing 10% lost to follow-up) we can detect: 25% reduction in excessive GWG from 80% to 60% (based on an 80% rate of excess weight gain in obese participants in the SCOPE study) [16] and 227 g difference in mean birthweight (based on CMH data; mean = 3,638, SD = 521). To allow for the two primary outcomes an alpha of 0.025 has been used for the power calculations (Bonferroni approach).

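### The fixed 0.025 threshold for both primary outcomes is valid, but Holm's step-down within each intervention keeps the same 5% limit and never rejects less (minor)

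*Protocol article*

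**What the plan says.** The protocol article names two primary outcomes, excessive GWG and infant birthweight. Its Statistical analysis plan section gives the decision rule: "For the primary outcomes a two-sided alpha level <0.025 will indicate statistical significance (Bonferroni adjustment". The Sample size and power calculation section plans on the same basis: "To allow for the two primary outcomes an alpha of 0.025 has been used for the power calculations (Bonferroni approach". Neither section describes a step-down rule.

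The rule is applied to two interventions. In the Randomisation section, women are "randomly allocated in a 1:1 ratio to dietary intervention or routine dietary advice; and 1:1 ratio to probiotic or placebo", and "Primary analyses will report marginal effects for each randomised exposure". That makes two primary tests per intervention and four in the trial. The closing paragraph of the Background hypothesises a reduction in one outcome, the other, or both.

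**The concern.** Under the fixed rule, each outcome must reach 0.025 whatever the other shows. A birthweight p-value of 0.03 would be declared non-significant even if excessive GWG had p < 0.001. Yet once one of two hypotheses has been rejected at 0.025, the other can be tested at 0.05 with the family-wise error for the pair still at or below 5%. Each outcome is powered at only about 80%, and an effect on both is among the trial's own hypotheses. What is at stake is the chance of confirming a second primary outcome after the first has succeeded.

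**Working it through.** **Inputs** (Sample size and power calculation): 220 women in total; 100 per main group left after 10% loss; 80% power; excessive GWG of 80% against 60%; a birthweight difference of 227 g with SD 521 g; alpha 0.025, taken as two-sided. Since 220 × 0.9 = 198, about 99 would remain per group at each margin; I use the plan's 100. The correlation between the two test statistics is not given, so I assume 0 to 0.5.

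**1. The plan's own figures** (normal approximation; critical values 2.2414 at 0.025 and 1.9600 at 0.05)

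GWG: null SE = √(2 × 0.7 × 0.3 / 100) = 0.06481; alternative SE = √((0.8 × 0.2 + 0.6 × 0.4) / 100) = 0.06325.
- At 0.025: Φ((0.20 − 2.2414 × 0.06481) / 0.06325) = **80.7%**
- At 0.05: Φ((0.20 − 1.9600 × 0.06481) / 0.06325) = 87.6%

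Birthweight: SE = 521 × √(2/100) = 73.68 g; 227 / 73.68 = 3.081.
- At 0.025: Φ(3.081 − 2.2414) = **79.9%** (79.4% with the t distribution)
- At 0.05: Φ(3.081 − 1.9600) = 86.9%
- Detectable difference at 80% power: 73.68 × (2.2414 + 0.8416) = 227.2 g

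The stated 80% power and 227 g both reproduce.

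**2. Error control of Holm for two outcomes**
- Both nulls true: a false claim needs the smaller p-value below 0.025, exactly as under Bonferroni, so the error is at most 5%.
- One null true: it can be rejected only if its own p-value is below 0.05, so the error is at most 5%.

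Neither step uses the correlation. Any p-value below 0.025 is rejected under both rules, so Holm never rejects less.

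**3. Power if both planned effects are real, correlation 0**
- GWG: 0.8066 + (0.8757 − 0.8066) × 0.7994 = 86.2%
- Birthweight: 0.7994 + (0.8688 − 0.7994) × 0.8066 = 85.5%
- Both, Bonferroni: 0.8066 × 0.7994 = 64.5%
- Both, Holm: 0.6448 + (0.0691 × 0.7994) + (0.8066 × 0.0694) = 75.6%
- At least one, either rule: 1 − (0.1934 × 0.2006) = 96.1%

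**4. Power at correlation 0.5** (simulation of bivariate normal statistics, 1,000,000 draws)

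| | Bonferroni | Holm | Gain, correlation 0.5 | Gain, correlation 0 |
|---|---|---|---|---|
| GWG | 80.7% | 85.1% | 4.4 | 5.5 |
| Birthweight | 79.9% | 84.5% | 4.6 | 5.6 |
| Both | 69.2% | 78.2% | 9.0 | 11.1 |

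The chance of succeeding on at least one is 91.5% under both rules at correlation 0.5.

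**5. If only one effect is real**
- If GWG is real and birthweight null, the gain in GWG power is (0.8757 − 0.8066) × 0.025 = 0.0017, about 0.2 points. The reverse case is the same to that precision.
- The false-positive rate for the null outcome rises from 2.5% to 0.025 + 0.025 × 0.8066 = 4.5%. It is 4.3% at correlation 0.5. With a larger effect on the first outcome it approaches the 5% ceiling.

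**6. All four tests**
- All nulls true: the bound is 4 × 0.025 = 10%, or 1 − 0.975⁴ = 9.6% if independent, under the plan. Holm within each intervention leaves the chance of any false claim unchanged here.
- Each intervention affecting one outcome only, factors treated as independent: the chance of at least one false claim is 1 − 0.975² = 4.9% under the plan and 1 − 0.955² = 8.8% under Holm within each intervention.

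**The case against.** The strongest reply is that nothing here is wrong. Bonferroni is valid, prespecified and stated alike in both sections, and the trial meets its 80% target with it. That stands. A reader might infer that the trial is underpowered or that its error control is faulty; the reproduced figures support neither.

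A reader might also infer that Holm is free in type I error. Only the 5% limit is unchanged. The error on a single null outcome rises from 2.5% to about 4.5%, and control remains per intervention. In the mixed case across four tests, the fixed threshold gives trial-wide protection (4.9%) that Holm gives up (8.8%). The plan does not claim trial-wide control, however: it explains 0.025 by the two outcomes alone.

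Nor is the gain general. It needs both effects at design size on the same intervention. For a claim on either outcome alone, Holm adds nothing to the chance of at least one success.

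Two practical points also stand. With a fixed 0.025, every test matches its 97.5% interval; under Holm, an outcome with p between 0.025 and 0.05 can be declared significant while its 97.5% interval includes no effect. Simple matching intervals are a legitimate reason to keep Bonferroni. And the Allocation concealment and blinding section says staff cannot be blinded to the dietary allocation, so a change made before unblinding has no clear meaning for that factor. The timing has to be tied to the first analysis by group.

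**Conclusion.** The point holds as a minor, cheap improvement. Within each intervention, Holm has the same 5% family-wise limit for the two primary outcomes, under any correlation, and rejects everything the plan's rule rejects. At the planned effects and 100 per group, it adds about 4 to 6 points of power per outcome and about 9 to 11 points for showing both. Those gains rest on both effects being real and on an assumed correlation of 0 to 0.5. The sample size and the stated 80% power are unaffected.

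**What to change.** Before any outcome data are analysed by group, replace the primary-outcome threshold with: *Within each intervention the two primary outcomes are tested by Holm: the smaller p-value at 0.025 and, if significant, the other at 0.05.* Keep the power calculation at 0.025 as the conservative planning case.

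Add that error control is per intervention and not across the four primary tests. Continue to report 97.5% intervals, and state that they need not agree with a decision taken at 0.05 in the second step.

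The cost is a dated amendment of a few lines. Sample size, data collection and models do not change, and as the Data management section plans no interim analysis, no interim boundary needs rework. Because this relaxes a published primary rule while the dietary comparison is open to staff, the amendment should record that no comparison by group had been seen.
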